# **1 Title of the clinical trial**

**1.1 Title of the clinical trial:** Efficacy of a music-therapy facilitated pulmonary telerehabilitation program in patients with chronic obstructive pulmonary disease: a multicenter, randomized controlled trial (COPDMELODY trial)

# **2 System for conducting research**

□ Single-site research

■ Multicenter study (Group name: **COPDMELODY**)

■ This institution is a principal investigative institution

□ Other institution is a principal investigative institution

**Role of Study Director**

The study director is in charge of the conception, planning, and preparation of the clinical trial protocol for this clinical trial in compliance with the Declaration of Helsinki and the ethical guidelines for clinical research, also supervises all work related to the study. The study director identifies the information necessary to anticipate risks and ensure safety and effectively guarantee adequate security until the study is completed, respect the dignity and human rights of individual subjects, and take the necessary actions to protect personal information. The study director reports necessary information to the heads of the participating institutions and to the ethics committee to assess adverse events and to ensure the appropriateness and reliability of the clinical study.

**Role of Investigators (in this institution)**

Investigators conduct the study based on the plan and work content specified in the study protocol and perform the work related to the study. Investigators are responsible for protecting the life, health, privacy, and dignity of the subjects based on the expertise and clinical experience necessary to properly conduct this research. Investigators provide the subjects with sufficient explanation of the necessary matters concerning the conduct of this research, and will obtain informed consent in writing from the subjects.

**Role of person responsible for allocation**

The person responsible for allocation prepares and keeps an allocation list prior to the start of the clinical trial. The subjects are randomly grouped according to this allocation table.

# **3 Introduction and objectives of the clinical trial**

**3.1 Introduction:** Chronic obstructive pulmonary disease (COPD) is the leading cause of morbidity and premature mortality globally, surpassing cancer, with the third-highest number of deaths in China, resulting in overwhelming pressure on healthcare systems(1). Moreover, living with COPD is often a daily struggle marked by reduced physical activity, further increasing disease progression, and creating a vicious circle (2). Psychologically, patients with COPD tend to suffer from increased stress and anxiety due to dyspnea and muscle dysfunction(3, 4).

Despite significant evidence on exercise capacity, symptoms and prognosis, the implementation of conventional pulmonary rehabilitation (PR) for COPD is insufficient, mainly due to inadequate resources, high cost, travel distance, lack of time, and low self-efficacy (5). Nonetheless, various telerehabilitation programs have been developed to overcome these barriers (6, 7). However, they play a limited role in reversing patients' low interests in exercises and rejection of rehabilitation due to fear of dyspnea and fatigue during training. Moreover, it is difficult to ensure the exact intensity of home-based exercises without professional equipment and real-time supervision (8, 9) and telerehabilitation programs with minimal equipment support are limited.

Recent studies have highlighted that music-facilitated rehabilitation not only benefits the interrelated physical and psychological consequences of patients but also improves motivation and training adherence. Music therapy (MT) targeting COPD includes passive (listening tomusic during aerobic exercises) and active elements (singing) (10, 11). Using rhythms to control the walking speed could offer an easy, economical way to ensure the exercise intensity at home. It can also be regarded as distractive auditory stimulus therapy, helping with dyspnea and fatigue during exertion (12). Additionally, singing promotes adaptation to breath control and training related respiratory muscles with less cost and more interest (13). Therefore, integrating tele-PR and MT may help overcome the previously mentioned barriers. However, there is a lack of relevant home-based studies as most of the existing studies were conducted in the hospital or community. Moreover there is limited evidence on the integrated effects of singing and music-guided aerobic exercises, with most studies only applying one kind of intervention (14).

Therefore, to identify a helpful and easy-to-use rehabilitation mode, our study aimed to develop a home-based, music-facilitated rehabilitation program for patients with COPD, using music tempo-guided walking exercises and breathing exercises, such as singing. Based on a thorough literature review, this is the first study to combine the two forms of MT for home-based PR and apply objective recording and supervision of training implementation using wearable sensors (a sports wristwatch that monitors step counts and walking distance) for music-facilitated tele-PR. This study protocol describes the process to investigate the efficacy and safety of the developed MT-facilitated telerehabilitation program (including rhythm-guided walking and singing).

**3.2 Objectives:** The primary aim of this study is to explore the efficacy of this home-based, MT- facilitated rehabilitation program (including rhythm-guided walking and singing). The secondary aim is to explore whether addition of singing training results in improvements compared with rhythm-guided walking alone.

# **4 Methods and duration of the study**

**4.1 study design**

This study will use a multi-center, prospective, three-arm, randomized controlled trial design. The study will include patients with COPD enrolled in a multi-module MT rehabilitation group (multi-module MT group), a rhythm-guided walking rehabilitation group (rhythm-guided walking group), and a usual care group. The study period will last for 12 weeks, and the outcomes will be measured at baseline (V0), 4 weeks (V1), 8 weeks (V2), and the end of intervention (V3). The study schedule and assessments are summarized in **Table 1.**

**Table 1.** Summary of study schedule

|  | **Enrolment** | **Baseline (V0)** | **4 weeks (V1)** | **8 weeks (V2)** | **12 weeks (V3)** |
| --- | --- | --- | --- | --- | --- |
| **Eligibility screening** |  |  |  |  |  |
| **Informed consent** | **√** |  |  |  |  |
| **Randomization** |  | **√** |  |  |  |
| **Allocation** |  | **√** |  |  |  |
| **Interventions** |  |  |  |  |  |
| **Multi-module music therapy** |  |  | | | |
| **Rhythm-guided Walking** |  |  | | | |
| **Usual care** |  |  | | | |
| **Assessments** |  |  |  |  |  |
| **Demographic characteristics** |  | **√** |  |  |  |
| **ISWT** |  | **√** | **√** | **√** | **√** |
| **MIP; MEP** |  | **√** | **√** | **√** | **√** |
| **Spirometry** |  | **√** |  |  | **√** |
| **SPPB** |  | **√** | **√** | **√** | **√** |
| **mMRC; CAT** |  | **√** | **√** | **√** | **√** |
| **SGRQ; EQ-5D** |  | **√** | **√** | **√** | **√** |
| **HADS** |  | **√** | **√** | **√** | **√** |
| **IPAQ** |  | **√** | **√** | **√** | **√** |
| **Training adherence** |  |  | **√** | **√** | **√** |
| **AEs** |  |  | **√** | **√** | **√** |

ISWT, incremental shuttle walking test; MIP, maximal inspiratory pressure; MEP, maximal expiratory pressure; SPPB, Short Physical Performance Battery; mMRC, Modified Medical Research Council; CAT, COPD assessment test; SGRQ, St. George's Respiratory Questionnaire; EQ-5D, EuroQoL-5D Questionnaire; HADS, Hospital Anxiety and Depression Scale; IPAQ, International Physical Activity Questionnaire; AE, adverse event.

**4.2 Study population and recruitment**

This multi-center study will be conducted at the China-Japan Friendship Hospital. Patients will be recruited from the China-Japan Friendship Hospital, Beijing Tiantan Hospital, Beijing Luhe Hospital, and the Second Affiliated Hospital of Xi'an Jiaotong University, Qingdao Municipal Hospital. Advertising strategies will include flyers within the hospital and professional recommendations. Potential eligible patients who are interested in participation will be invited to have either a face-to-face or telephone meeting wherein the researchers will explain the study in detail and allow time for questions. Potential patients will be asked about medical history and undergo a pulmonary function test to ensure final eligibility. The inclusion and exclusion criteria are summarized in **Table 2**. Patients who meet the eligibility criteria will be invited to sign informed consent forms and complete baseline outcome assessment.

**Table 2.** Inclusion and exclusion criteria

| **Inclusion Criteria** | **Exclusion Criteria** |
| --- | --- |
| 1. Adults aged 40−75 years. | 1. Acute myocardial infarction within 4 weeks, unstable angina, uncontrolled atrial or ventricular arrhythmia, and heart failure. |
| 2. Diagnosed with COPD of GOLD II-IV. | 2. Hypertrophic cardiomyopathy, severe valvular heart disease, severe aortic stenosis. |
| 3. Current outpatient, stable for at least 2 weeks prior to the intervention enrolment. | 3. Acute pulmonary embolism, uncontrolled asthma, respiratory failure. |
| 4. Able to use a smartphone. | 4. Comorbidity precluding exercise training (e.g., orthopedic, neurological, or cognitive conditions). |
| 5. Able to understand the purpose of the clinical trial and voluntarily participate with signed informed consent. | 5. Presence of malignant tumor. |
|  | 6. Involved in pulmonary rehabilitation programs within the past 12 months. |

**4.3 Randomization, allocation concealment, and blinding**

All patients will be randomized in a 1:1:1 ratio (adhering to block randomization within each center) into three groups: Multi-module MT, rhythm-guided walking, and usual care groups using a table of random numbers generated in the SPSS statistical package held by an independent statistical analyst. Group information will be stored in an opaque envelope and sealed thereafter. After obtaining informed consent and baseline assessment, the study coordinator will unseal the envelope to obtain the random numbers and grouping information for each participant.

Due to the nature of the intervention, neither the participants nor the exercise instructors will be blinded. However, pulmonology and rehabilitation nurses conducting outcome assessments and statistical analysts will be blinded to the assignments.

**4.4 Interventions**

All patients will continue taking routine medications, such as bronchodilators and steroid inhalers, according to their respective conditions and will maintain their regular treatment visits throughout the study period. Additionally, patients in the two intervention groups will receive two different forms of PR programs conducted by a multi-disciplinary team consisting of pulmonologists, rehabilitation physicians, pulmonology and rehabilitation nurses, music therapists, and research assistants **(Tables 3 and 4)**. The 12-week PR program is based on exercise, facilitated with music.

Home-based rehabilitation prescriptions will be conveyed by a software installed on the smartphone, containing different function modules based on the intervention group. Each patient will be provided a secure user account to log into the software.

### **4.4.1 Multi-model MT group**

Participants in the multi-model MT group will undergo two types of training: rhythm-guided walking (aerobic exercises) and singing (respiratory muscle training). Additionally, their softwares will contain two function modules: the “rhythm-guided walking” module which includes melodies with various rhythms (60−120 bpm) that can match individual walking speeds and the “singing” module which includes various songs suitable for patients to sing, which are selected and recorded by music therapists.

The participants will undertake three walking sessions of at least 30 min per week. The exercise intensity (in the form of walking speed) will be prescribed individually, according to the ISWT results. The peak walking speed (v_peak) will be assessed by the ISWT, and the targeted training speed will be set at 75%, according to the American College of Sports Medicine. A music rhythm (i.e., stride frequency) matching the target speed will be calculated using the following formula:

[figure not shown]
 (1)

[figure not shown]
 (2)

Patients will be asked to follow this individualized music rhythm and walk at a fixed pace to maintain a constant speed. During the aerobic exercise, patients will need to open the "rhythm-guided walking" module on the software, to play the melodies with the prescribed specific tempo on a loop. Patients will need to regulate their stride frequency corresponding to the tempo to achieve adequate exercise intensity. During this, they will be asked to wear a sports wristwatch displaying their walking distance.

Additionally, the participants will undertake three singing sessions of at least 25 min per week, following the prescriptions conveyed by the software. One session includes 10 min of breathing exercises and vocal warm-up with a focus on awareness of supporting musculature during inhalation and exhalation, as well as subconscious vocal release before singing songs. It rounds up with 15 min of singing songs to improve the strength, endurance, and flexibility of the respiratory muscles. During the respiratory muscle training, patients need to open the "sing" module to follow the guiding audios and videos.

**Table 3.** Multi-module MT rehabilitation program

| **Aerobic training** |  |
| --- | --- |
| - **Rhythm-guided walking** | Exercise at an intensity of 75% of the patients' peak speed evaluated by ISWT. |
|  | Walking at a fixed pace following the music tempo matched with the targeted speed. |
| **Duration** | 30 min |
| **Respiratory muscle training** |  |
| - **Breathing exercise** - **Vocal warm-up** - **Singing songs** | Breathing control, pursed lips breathing, and abdominal breathing.  Introducing 'primal sounds' such as Hey, Ho, Ha, etc.,  Choosing appropriate songs fit for patients in terms of phrase lengths, breath points, lyrics, melodic challenge, and range. |
| **Duration** | 25 min |

MT, music therapy; ISWT, incremental shuttle walking test

### **4.4.2 Rhythm-guided walking group**

Participants in the rhythm-guided walking group will perform only music-facilitated walking exercises as previously described in the multi-module MT group.

**Table 4.** Rhythm-guided walking rehabilitation program

| **Aerobic training** |  |
| --- | --- |
| - **Rhythm-guided walking** | Exercise at an intensity of 75% of the patients' peak speed evaluated by ISWT. |
|  | Walking at a fixed pace following the music tempo matched with the targeted speed. |
| **Duration** | 30 min |

ISWT, incremental shuttle walking test

### **4.4.3 Usual care group (Waiting-list control group)**

During the study period, patients in the usual care group will not receive any rehabilitation intervention during the 12-week study period. However, they will be invited to access the music-facilitated PR program once the follow-up test is complete, thus, establishing a waiting-list control group.

**4.5 Outcome measures**

**Table 1** illustrates the items to be measured and the time window for data collection. The primary outcome is the exercise capacity measured by ISWT in all three subgroups. The ISWT will be determined according to the recommendations of the European Respiratory Society/American Thoracic Society (15). In addition, as an externally paced maximal exercise test, walking speed will be controlled by a series of pre-recorded signals. The walking speed increases progressively until the participant can no longer continue.

The secondary outcomes are:

1. Respiratory muscle function: This will be assessed by the maximal inspiratory and expiratory pressures using the Gio Digital Pressure Gauge (16).

2. Pulmonary function test: This will be assessed by spirometry performed using automated equipment as the guideline (17).

3. Lower Extremity Function: This will be assessed using the Short Physical Performance Battery (SPPB), an objective tool for measuring lower extremity physical performance status. The SPPB is based on three timed tasks: standing balance, walking speed, and chair-stand tests (18).

4. Symptoms: Chronic activity-related dyspnea will be assessed using the modified Medical Research Council dyspnea scale (mMRC). The respiratory health status will be assessed using the COPD Assessment Test (CAT).

5. Health-related quality of life (HRQoL): This will be measured using St. George's Respiratory Questionnaire (SGRQ) (19, 20) and the EuroQoL-5D Questionnaire (EQ-5D)(21). These are simple, generic HRQoL instruments widely used as patient-reported outcome measures.

6. Anxiety/depression rates: This will be evaluated in the hospital using the Hospital Anxiety and Depression Scale (HADS) which comprises seven items each for the anxiety and depression subscales. The HADS is a validated measure for assessing anxiety and depression symptoms and is recommended for patients with COPD (22, 23).

7. Physical Activity (PA) level: Daily PA will be measured using the International Physical Activity Questionnaire (IPAQ) adopted in Chinese, which presents acceptable reliability and high repeatability values (24).

8. Training adherence: Patient training adherence is defined as the percentage of the total number of completed training sessions. The supervising hospital staff will record patient adherence.

9. Safety measurements: All adverse events (AEs) that occur during the study will be recorded and evaluated for relevance to the intervention. AEs include exacerbations, exercise injuries, and falls

**4.6 Data management and quality control**

Patients will be required to practice rhythm-guided walking or singing until they master it on their first hospital visit. Telephone calls or video conferences by rehabilitation instructors will be integrated at the start of the program to ensure proper execution. After each training session, participant performance will be automatically transferred to the digital platform to facilitate the identification and verification of adherence to the prescribed exercise plan. Research assistants will verify training completion every day, record training adherence, and remind the patients to exercise.

To decrease measurement error, each participant will be assessed by a single researcher during different visits. Study data will be maintained on a password-protected platform and backed up to a secure external hard drive, with access restricted to authorized researchers and staff. Automatic plausibility controls will be set to detect any inconsistencies or inaccuracies during data entry.

**4.7 Statistical analysis methods and sample size calculation**

### **4.7.1 Statistical analysis methods**

The primary analysis will be conducted as intention-to-treat (ITT), including all patients that received randomization. Continuous baseline characteristics are given as median (range) or mean (SD) as appropriate and categorical variables as frequencies. Three comparisons will be carried out: multi-module MT versus usual care, multi-module MT versus rhythm-guided walking and rhythm-guided walking versus usual care. All analyses will be carried out using two-sided significance tests at the 0.05 significance level. Our primary analysis will compare the treatment groups at 12 weeks. The primary outcome, ISWT distance, will be analyzed using a linear mixed model, including assessments at all available time points with reference to the date of randomization. The model will include treatment group, time point of measurement as fixed effects. Other covariates treated as fixed effects were the treatment by time point interaction, age (in years), gender (male or female), BMI and ISWT at baseline. The model included recruitment site as a random effect. The model will provide treatment group differences over 12 weeks as well as estimates at individual time points. These will be presented as mean estimates with 95% confidence intervals and associated p values. For the modelling of repeated measurements, the best fitting (based on AIC and BIC information criteria), simple (not significantly different from an unstructured pattern) covariance pattern will be selected. Model assumptions will be checked and, if they are in doubt, the data will be transformed prior to analysis or alternative non-parametric analysis methods will be used. The following outcomes will be analyzed analogously to the evaluation described above for the primary outcome : mMRC scores, quality of life measures, and anxiety/depression rate, MIP/MEP and pulmonary function parameters.

Two separate sensitivity analyses will be undertaken: multiple imputation for missing data, inclusion of participants receiving the randomly assigned treatment and completing the study (i.e., a per-protocol population).

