### **4.7.2 Sample size**

Considering the lack of previous studies combining music-guided walking with singing, we calculated a sample size based on studies applying similar rehabilitation interventions(25, 26). The primary outcome is the distance of ISWT and the sample size was based on change in our primary outcome from baseline to week 12. As suggested by similar studies, we assumed mean changes of multi-model MT group, rhythm-guided walking group and usual care group are 40 m, 27 m, and -15m, respectively(25, 26), and the combined standard deviations (SD) are 35 m, 38 m, and 40 m, respectively. A sample size of 9 patients per group yields a power of 90% at a 2-sided significance level of 5% with an ANOVA. Adjusting for approximately 50% dropout results in a target group size of 18 participants per study group and a total case number of 54.

[figure not shown]

Therefore, 75 participants are anticipated to be enrolled into this study.

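### Section 4.7.1 tests three contrasts of the primary outcome, each at 0.05, without carrying the ranking of aims in section 3.2 into a named primary contrast or testing rule

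*Protocol*

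**What the plan says.** Section 4.7.1 of the protocol sets out the comparisons: "Three comparisons will be carried out: multi-module MT versus usual care, multi-module MT versus rhythm-guided walking and rhythm-guided walking versus usual care". It then fixes the error rule for all of them: "All analyses will be carried out using two-sided significance tests at the 0.05 significance level". The primary analysis is tied to a time point but not to a contrast: "Our primary analysis will compare the treatment groups at 12 weeks". Section 4.5 likewise defines the primary outcome across arms: "The primary outcome is the exercise capacity measured by ISWT in all three subgroups".

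The protocol does rank its questions, but elsewhere. In section 3.2, "The primary aim of this study is to explore the efficacy of this home-based" refers to the programme that combines rhythm-guided walking and singing; no comparator is named. Then: "The secondary aim is to explore whether addition of singing training results in improvements compared with rhythm-guided walking alone". Walking versus usual care appears under neither aim. Section 4.7.2 sizes the trial on a three-group ANOVA, but 4.7.1 does not use that test as a gate before the pairwise comparisons.

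**The concern.** Section 3.2 has an order and section 4.7.1 does not. In the analysis section the three contrasts have equal standing on the primary outcome, each at the full 0.05, including one that belongs to no stated aim. If only one of the three comes out significant, nothing in 4.7.1 says whether the trial has met its primary objective or has produced a secondary finding. The 5% stated in the plan is then the error rate of each test and not of the set of three.

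This goes beyond a detail that a statistical analysis plan would normally supply. The protocol itself states the error rule for every analysis, directly after listing the three contrasts. A later plan that imposed a hierarchy would have to narrow that sentence.

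**Working it through.** **Inputs.** Three contrasts, each at two-sided 0.05 (section 4.7.1). Equal allocation: "All patients will be randomized in a 1:1:1 ratio" (section 4.3). For power: "we assumed mean changes of multi-model MT group, rhythm-guided walking group and usual care group are 40 m, 27 m, and -15m", with SDs of 35, 38 and 40 m (section 4.7.2). Group sizes: 9 and 18 are stated in 4.7.2, and 25 is the 75 planned divided by three. Twelve per group is an assumption of this check: 25 × (1 − 0.5) = 12.5 after the protocol's approximate 50% dropout, rounded down. The protocol states no familywise error rate, so there is no figure of its own to reproduce.

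**Step 1: error over the three tests when all arms are equal.** The tests share arms, so they are correlated. With n per arm, a pooled variance and df = 3n − 3, at least one pairwise test is significant exactly when the range of the three means is large enough:

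P(any p < 0.05) = P(Q > √2 × t), where Q is the studentized range for three means on df degrees of freedom and t is the 97.5% point of the t distribution on df.

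| n per arm | df | t | √2 × t | P(any) |
|---|---|---|---|---|
| 9 | 24 | 2.064 | 2.919 | 11.9% |
| 18 | 51 | 2.008 | 2.839 | 12.1% |
| 25 | 72 | 1.993 | 2.819 | 12.1% |
| large | ∞ | 1.960 | 2.772 | 12.2% |

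Simulation agrees (12.2% for large samples). Treating the tests as independent would give 1 − 0.95³ = 14.3%, which is too high.

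**Step 2: favourable directions only.** Counting only MT better than usual care, MT better than walking, or walking better than usual care, simulation gives 6.5% to 6.6%. The matching figure for one two-sided 0.05 test is 0.05/2 = 2.5%.

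**Step 3: does a gate on MT versus usual care control the error?**
- If MT and usual care are truly equal, no other contrast is tested unless this true null is rejected. That happens with probability 5%, so the error over all three tests is 5%.
- If MT and usual care truly differ, MT = walking and walking = usual care cannot both hold, since together they would make MT equal to usual care. At most one true null remains, tested at 0.05.

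In both cases the familywise error is at most 5%, and the two secondary contrasts need no order between them.

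**Step 4: power cost.** Simulated t tests using the variance pooled over the three arms and the protocol's means and SDs:

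| Contrast | 12 per group: unadjusted | gated on MT vs usual care | 25 per group: unadjusted | gated |
|---|---|---|---|---|
| MT vs usual care | 93.5% | 93.5% | 99.9% | 99.9% |
| MT vs walking | 12.1% | 12.0% | about 22% | about 22% |
| Walking vs usual care | 75% | 73% | 96.9% | 96.8% |

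**Step 5: two alternatives.** Requiring a significant omnibus F test first also holds about 5% (4.9% to 5.1% simulated), but it lowers power for MT versus usual care from 93.5% to 88.8% at 12 per group. A strict sequence that puts walking versus usual care second and MT versus walking last cuts MT versus walking from 12.1% to 6.0% at 12 per group. It would also place a contrast with no stated aim ahead of the stated secondary aim.

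**The case against.** The strongest reply is that the ranking already exists. Section 3.2 makes the combined programme primary and the addition of singing secondary. If MT versus usual care is read as the primary contrast, its own error rate is 5%. Both aims are worded as exploration, the contrasts answer different questions about different programmes, and whether such questions need familywise control is debated. A testing order is also often left to a statistical analysis plan, which may exist.

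Much of this stands, and it limits the point in three ways:

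- A reader might infer that the protocol ranks nothing. It does rank its aims. The gap is that 4.7.1 does not translate the ranking into a contrast, and that the primary aim names no comparator.
- A reader might infer a 12% chance of a false efficacy claim. The 12% includes results in which usual care beats MT or walking beats MT, which nobody would claim as efficacy. The favourable-only figure is about 6.5%.
- A reader might infer that any one of the three results would establish the programme's efficacy. Under section 3.2, walking versus usual care does not answer the primary aim.

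The appeal to a separate analysis plan does not stand in full, because the protocol has already set 0.05 for every analysis. Exploratory wording also sits uneasily with a named primary outcome and a sample size set for 90% power at a 5% level.

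**Conclusion.** The point holds in this limited form and should be fixed. Across the three primary-outcome tests as written, the chance of at least one false significant difference is about 12% when all arms are equal, or about 6.5% in favourable directions. The correct single-test comparators are 5% and 2.5%, so the inflation is roughly two and a half times in each case (12/5 = 2.4; 6.5/2.5 = 2.6).

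The error figures assume equal arm sizes, a common variance and no true difference between any arms. The power figures come from simple pooled-variance tests, not from the planned mixed model with baseline ISWT as a covariate, so they show the relative cost of the rules and do not predict the trial's power. Reading MT versus usual care as the primary question is an inference from section 3.2, since MT versus walking is expressly secondary there; the sponsor should confirm it.

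**What to change.** In section 4.7.1, add two sentences to this effect:

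- The single primary comparison is multi-module MT versus usual care in ISWT distance at week 12, tested at two-sided 0.05.
- MT versus walking (the secondary aim) and walking versus usual care are secondary. Each is tested at two-sided 0.05 only if the primary comparison is significant; otherwise each is reported as an estimate with its 95% confidence interval and no claim of significance.

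Section 3.2 should name usual care as the comparator for the primary aim, so that the two sections agree. The change should be made before anyone sees unblinded outcome data.

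The cost is wording only. The primary contrast loses no power. At the assumed 12 per group, MT versus walking loses about 0.1 percentage point and walking versus usual care about 2; at 25 per group the losses are negligible. An omnibus gate is a valid alternative but not an equivalent one, because it takes about 5 points of power from the primary contrast at 12 per group. No rule for testing order cures the low power for MT versus walking, which is about 12% at 12 per group even unadjusted.

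### The covariance pattern of the primary ISWT model is picked from the data using a weak test, which can bias the week-12 standard error in either direction

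*Protocol*

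**What the plan says.** Protocol section 4.7.1 analyses ISWT distance with a linear mixed model over the repeated visits. The time point that counts is fixed: "Our primary analysis will compare the treatment groups at 12 weeks". The level is fixed too: "All analyses will be carried out using two-sided significance tests at the 0.05 significance level". Besides group and time, the fixed effects are "the treatment by time point interaction, age (in years), gender (male or female), BMI and ISWT at baseline", and recruitment site is a random effect.

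The within-patient covariance is not fixed. It is to be "the best fitting (based on AIC and BIC information criteria"), and a "simple (not significantly different from an unstructured pattern) covariance pattern will be selected". Several secondary outcomes follow the same analysis.

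Section 4.1 sets the visits: "outcomes will be measured at baseline (V0), 4 weeks (V1), 8 weeks (V2), and the end of intervention (V3"). Section 4.7.2 sets the size: "Adjusting for approximately 50% dropout results in a target group size of 18 participants per study group and a total case number of 54". It then anticipates 75 enrolled. Its SDs (35, 38 and 40 m) are by arm, for the change from baseline to week 12. No SDs by visit are given.

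**The concern.** The rule treats a non-significant test against unstructured as support for a simpler pattern. In a small trial with heavy dropout, such a result says little.

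The choice matters because the primary comparison is at one visit. Equal-variance patterns (compound symmetry, AR(1)) estimate the week-12 variance by pooling all follow-up visits, and under dropout the earlier visits contribute more patients. If the spread of ISWT differs between visits, the pooled variance is wrong for week 12, and so are the interval and p value of the primary result. This is separate from any multiplicity across the three comparisons. The same data also choose the pattern and supply the p value.

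**Working it through.** **Inputs from the protocol.** Three arms, 1:1:1 (4.3); follow-up at weeks 4, 8 and 12 (4.1); two-sided 5% level and the model terms (4.7.1); 9 evaluable per group, about 50% dropout, 54 or 75 patients (4.7.2).

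**Plan's own figure.** 9 / (1 - 0.5) = 18 per arm, and 3 x 18 = 54, so the dropout step reproduces. 75 / 3 = 25 per arm.

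**Assumed, because the protocol is silent.** SDs by visit, within-patient correlation, timing of dropout and candidate patterns. A week-12 SD of 38 m matches the protocol's by-arm SDs. Baseline ISWT is taken as a covariate only, so there are three responses per patient and an unstructured matrix has 3 x 4 / 2 = 6 parameters.

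**Rough size of the bias once an equal-variance pattern is used.** Suppose 15, 12 and 9 patients per arm remain at weeks 4, 8 and 12.
- SDs 30/34/38 m: pooled variance = (15 x 900 + 12 x 1156 + 9 x 1444) / 36 = 40368 / 36 = 1121, so SD 33.5 m. Against 38 m the ratio is 0.88 (too small).
- SDs 38/34/30 m: (15 x 1444 + 12 x 1156 + 9 x 900) / 36 = 43632 / 36 = 1212, so SD 34.8 m. Against 30 m the ratio is 1.16 (too large).

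The direction therefore depends entirely on how the SD moves. The average bias under the rule is smaller, because the rule does not always end on an equal-variance pattern.

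**Simulation of the rule.** Null trials with 50% dropout and REML fits of CS, AR(1), heterogeneous CS, heterogeneous AR(1) and unstructured. Patterns with likelihood-ratio p > 0.05 against unstructured are kept, then the lowest AIC or lowest BIC is taken. Runs 1 and 2 include baseline and three covariates and use Satterthwaite degrees of freedom. Type I error for one week-12 contrast, SDs 30/34/38 m:

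| Run | Per arm | Correlation | AIC choice | BIC choice | Always unstructured |
|---|---|---|---|---|---|
| 1 (800-1,000 trials) | 18 | AR 0.5 | 6.8% | 8.5% | 5.3% |
| 1 | 18 | AR 0.7 | 6.7% | 7.9% | 5.2% |
| 2 (2,500 trials) | 18 | AR 0.5 | 7.4% | 8.6% | 5.9% |
| 2 | 18 | AR 0.7 | 7.3% | 7.8% | 5.7% |
| 3 (2,000 trials) | 18 | range over scenarios | 6.1-6.6% | 7.2-8.2% | 4.8-5.5% |
| 1 | 25 | AR 0.5 | 6.1% | 7.2% | 4.9% |
| 2 | 25 | AR 0.5 | 5.8% | 6.8% | 5.2% |

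Monte Carlo error is about 0.5 to 0.9 points. At 18 per arm, the rule ended on an equal-variance pattern in 45-60% of trials by AIC and 74-82% by BIC (runs 2 and 3). The BIC-choice standard error averaged 0.90-0.91 of the true one, against 0.96-0.97 with unstructured (runs 1 and 2).

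**Other variance profiles, 18 per arm.**
- Falling (38/34/30 m, AR 0.6, run 2): standard error about 7% too large under BIC, type I error 3.6% against 5.0% with unstructured. Run 3, also with falling SDs: 6-8% too large, type I error 3.9%.
- Equal: 5.7-5.8% under the rule, 6.1% with unstructured (run 2). The rule is valid.
- Near doubling (19/28/38 m, correlation 0.7, run 4, described under the objection): an equal-variance pattern is chosen in 0-2% of trials.

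**Cost of always using unstructured when variances are equal (run 1).** Power under BIC choice against unstructured is 67% v 66% and 63% v 63% for a 42 m difference (27 + 15), and 87% v 87% and 84% v 82% for 55 m (40 + 15). Before rounding, the loss is about 0-1.5 points.

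**The case against.** The strongest reply is that the harm is conditional and modest. No visit SDs are given, so rising variance is an assumption.

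The size also depends on analysis details that the protocol does not set. Run 4 (1,000 trials per scenario) left out age, gender and BMI and used week-12 completers minus 4 as degrees of freedom. With 54 patients its type I error under the rule was 4.4-4.7% at 32/35/38 m. At 27/32/38 m it was 4.1-5.0% with correlation 0.7, and 5.9-8.3% with correlation 0.4. Putting those degrees of freedom into run 2 lowers the BIC results by 0.7-1.1 points (8.6% to 7.5%, for example). With 75 patients and 20% dropout at 27/32/38 m, an equal-variance pattern is chosen in only 3-16% of trials, and the standard error is 0.97-0.99 of the true one.

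Information-criterion selection checked against unstructured is also a recognised approach, heterogeneous patterns are not excluded, model assumptions are to be checked, and an unseen SAP may list candidates and degrees of freedom.

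These points stand as limits on size. They do not remove the concern, because the protocol itself states the selection rule, and replacing it costs little.

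One objection to the remedy also stands. The simulations did not test convergence of an unstructured model with the planned random site effect, at about 9 week-12 completers per arm.

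**Conclusion.** The point holds in conditional form. At the planned size the rule often keeps an equal-variance pattern when visit SDs differ mildly to moderately, and the week-12 standard error is then biased. With SDs rising as in 30/34/38 m and 50% dropout, type I error is about 6-7% (AIC) or 7-8.5% (BIC), against about 5% with unstructured. With falling SDs the analysis is conservative, at about 4% under BIC. With equal SDs there is no harm. All of this rests on assumed SDs by visit, assumed correlations and simulations without a site effect.

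A reader might infer more, and the documents do not support it:
- That the rule makes the standard error too small. This needs variance rising to week 12, which the protocol neither states nor implies.
- That it usually misses unequal variances. That is true for mild inequality, but at 27/32/38 m with correlation 0.7 run 4 chose an equal-variance pattern in 21-51% of trials, and a near doubling is rarely missed.
- That shortfalls of 15-26% are in play. Those come from forcing compound symmetry whatever the data show, which the rule does not do.

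This is a cheap improvement of low to moderate priority. It does not invalidate the primary analysis.

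**What to change.** Replace the selection rule in section 4.7.1 with wording such as: *ISWT at weeks 4, 8 and 12 will be modelled with an unstructured within-patient covariance matrix and Kenward-Roger (or Satterthwaite) degrees of freedom. If this model does not converge, including with the random site effect, the following patterns will be tried in order and the first that converges will be used: heterogeneous Toeplitz, then heterogeneous AR(1).*

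Delete the significance test and the AIC/BIC choice. Apply the same rule to the secondary outcomes analysed in the same way and measured at every visit. Spirometry is measured only at baseline and week 12 (Table 1), so it has no repeated follow-up to model.

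The cost is a short wording change, with no extra data or patients, and about 0-1.5 points of power if the visit variances are truly equal. Convergence with the site effect should be checked on simulated data before the wording is final.
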